#### 2.4.2. Aim 1: quantitative data analysis

We will compare the effect of the V-DPP-TOAT versus the DPP-TOAT interventions on weight and glycemia, which are both continuous outcomes. First, we will report means and standard deviations by randomization assignment and assess the assumption of normality in the outcomes. We will estimate the model using ordinary least squares regression
$$Y6_{i}=\beta_{0}+\alpha_{0}Y0_{i}+\alpha_{1}P_{i}+e_{i}$$
where 
$Y6_{i}$
 is the 6-month weight or Hemoglobin A1c for participant 
i
. 
$Y0_{i}$
 is the baseline weight or A1c for participant 
i
. 
$P_{i}$
 is an indicator variable, where 
$P_{i}=1$
 if the participant 
i
 has been randomized to V-DPP-TOAT, and 
$P_{i}=0$
 for the DPP-TOAT. 
$e_{i}$
 is an error term. The parameters to be estimated are as follows: 
$\beta_{0}$
 is the average for those in the DPP-TOAT group; 
$\alpha_{0}$
 represents the relationship between the baseline and follow-up outcome (weight or A1c) measurement; if the relationship is strong, the inclusion of the baseline measurement can increase statistical power; and 
$\alpha_{1}$
 represents the effect of the V-DPP-TOAT intervention. Specifically, the hypothesis test will compare 
$H_{0}:\alpha_{1}<\Delta$
 vs. 
$H_{A}:\alpha_{1}\geq -\Delta$
 with the noninferiority margin 
Δ
 set as 5% for each of the outcomes. We will calculate the 95% confidence interval of 
$\alpha_{1}$
. If the lower bound is above the margin -Δ, the V-DPP-TOAT is deemed non-inferior and the trial is a “success.” Further, if the lower bound of that same CI is also above zero, then superiority of V-DPP-TOAT can also be declared (41). Interaction terms between 
$Y0_{i}$
 and 
$P_{i}$
 will be tested to see if there is effect modification by any of the baseline covariates.

We will assess heterogeneity in outcomes among healthcare settings/clinics by estimating an intraclass correlation coefficient (ICC). If the heterogeneity cannot be ignored, we will use a multi-level model with nested random effects in the above equation to accommodate the correlations caused by healthcare settings/centers. Outcomes analysis will use an intention-to-treat principle, with a per-protocol analysis as a sensitivity analysis (41) employing R software (version 1.2.5019, R Foundation for Statistical Computing) for all analyses.

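### The Aim 1 decision rule runs in the wrong direction for the model as printed: the outcome is 6-month weight or A1c, where higher is worse, but success is read from the lower confidence bound

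*Protocol article*

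**What the plan says.** Protocol article, section 2.4.2 (Aim 1: quantitative data analysis), sets out one regression for weight and for A1c:

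- The outcome Y6 "is the 6-month weight or Hemoglobin A1c for participant" i, and the covariate Y0 "is the baseline weight or A1c for participant" i. Both are absolute values, not losses or changes.
- The indicator P is 1 for V-DPP-TOAT and 0 for DPP-TOAT, and α₁ is its coefficient.
- The margin Δ is "set as 5% for each of the outcomes".
- The decision rule: "If the lower bound is above the margin -Δ, the V-DPP-TOAT is deemed non-inferior". For superiority: "if the lower bound of that same CI is also above zero, then superiority of V-DPP-TOAT can also be declared".
- The hypotheses are printed as H₀: α₁ < Δ against H_A: α₁ ≥ −Δ.

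Two other places use a different scale. The abstract names weight loss at 6 months as the primary effectiveness outcome. Section 2.4.2.2 (Power: aim 1) gives the planning values as weight losses, 5 kg virtual and 6.6 kg in-person with SD 5 kg. It describes a one-sided test on the lower bound and puts the margin at 5% of the in-person weight loss.

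**The concern.** With Y6 as the outcome and P = 1 for the virtual arm, α₁ is virtual minus in-person on a scale where higher is worse. A lower bound above zero is then evidence that virtual participants are heavier, or have higher A1c, at 6 months. The article labels that result superiority of the virtual arm. The non-inferiority rule is turned round in the same way: it guards against the virtual arm being too light, not too heavy.

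This is the rule for the primary effectiveness claim. Applied as printed, it rewards a worse virtual arm and can refuse a better one.

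**Working it through.** **1. Sign of α₁.** The model is Y6 = β₀ + α₀Y0 + α₁P + e. Subtracting Y0 from both sides gives Y6 − Y0 = β₀ + (α₀ − 1)Y0 + α₁P + e, so baseline adjustment or analysing the change leaves α₁ unaltered. Only reversing the outcome does so: for the reduction Y0 − Y6 the coefficient of P is −α₁.

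**2. Inputs** (section 2.4.2.2 unless stated).
- Losses of 5 kg virtual and 6.6 kg in-person: the virtual arm is 1.6 kg heavier at equal baseline, so α₁ = +1.6 kg.
- SD 5 kg, 85 per group.
- Δ = 0.05 × 6.6 = 0.33 kg.
- 95% interval (section 2.4.2), taken as two-sided, z = 1.96.
- SE = 5 × √(2/85) = 0.767 kg (normal approximation, no gain from baseline adjustment).

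**3. The plan's own sample size.** n = 2 × SD² × (z₀.₉₅ + z₀.₈₀)² / distance².
- 1.6 kg added to the margin: distance 0.33 + 1.6 = 1.93 kg, and n = 2 × 25 × (1.645 + 0.842)² / 1.93² = 83 per group (84 by t-test), against 85 stated. For attrition, 85/0.75 gives 114 per arm, 228 in total, against 230 stated.
- Correct direction: 0.33 − 1.6 = −1.27 kg. The assumed truth is already outside the margin. Power at 85 per group is Φ(−1.27/0.767 − 1.645) = 0.0005, and no sample size reaches 80%.

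So, with the stated margin, 85 per group is recovered when the 1.6 kg counts in favour of the virtual arm.

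**4. Operating characteristics.**
- Written rule: P(non-inferior) = Φ((α₁ + Δ)/SE − 1.96); P(superior) = Φ(α₁/SE − 1.96).
- Corrected rule (upper bound below +Δ, or below 0): P(non-inferior) = Φ((Δ − α₁)/SE − 1.96); P(superior) = Φ(−α₁/SE − 1.96).

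| True α₁ | Written: non-inferior | Written: superior | Corrected: non-inferior | Corrected: superior |
|---|---|---|---|---|
| +1.6 kg (virtual worse, as planned) | 0.71 | 0.55 | 0.0001 | <0.0001 |
| 0 | 0.063 | 0.025 | 0.063 | 0.025 |
| −1.6 kg (virtual better) | 0.0001 | <0.0001 | 0.71 | 0.55 |

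For the first row: Φ(1.93/0.767 − 1.96) = 0.71 and Φ(1.6/0.767 − 1.96) = 0.55. At one-sided 0.05, the level in the power section, these become 0.81 and 0.67. The superiority figures do not depend on Δ.

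**The case against.** The strongest reply is that the authors meant weight loss. The abstract says so, the power section is written in losses, and on that scale the lower-bound rule is correct. An analyst would probably notice before calling a heavier arm superior. This stands as a reading of intent for weight. It does not correct the printed equation, to whose coefficient the rule is tied, and it does not reach A1c, for which the article gives no reduction scale.

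Four stronger readings are tempting, and the article does not support them.

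- **That the trial's conclusion will be reversed.** This follows only if section 2.4.2 is applied literally. The weight-loss wording elsewhere leaves room for the intended analysis.
- **That any better virtual arm must fail.** This depends on Δ. At 0.33 kg, an arm 1.6 kg better passes about 0.01% of the time. If Δ were 3.5 kg (5% of an assumed 70 kg body weight, a figure not in the article), the same arm would pass with probability Φ((3.5 − 1.6)/0.767 − 1.96) = 0.70.
- **That the sample size proves a sign error.** The reproduction is not unique: a 3.5 kg margin in the correct direction gives 86 per group. That margin conflicts with the one stated in section 2.4.2.2, but the possibility rules out proof.
- **That the overlapping hypotheses are a second independent fault.** As printed, both hold for α₁ from −Δ up to Δ. The null probably lost a minus sign, in print or in text extraction, and the decision rule itself uses −Δ. The hypotheses need restating but add little weight.

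**Conclusion.** The point holds. The article prints the outcome, the arm coding and the decision rule, and together they are wrong; this is not detail left to an analysis plan. Under the plan's own assumption that the virtual arm loses 1.6 kg less, the written rule calls it non-inferior with probability 0.71 and superior with probability 0.55, where a correctly directed rule gives about 0.0001 and less than 0.0001. These figures rest on SD 5 kg, 85 per arm, a two-sided 95% interval and, for non-inferiority only, Δ = 0.33 kg. A smaller residual SD from baseline adjustment would make the error larger at the assumed difference. It must be fixed, because it governs the primary effectiveness claim and the weight-loss wording elsewhere resolves it neither for the printed model nor for A1c.

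**What to change.** Choose one form and use it for both outcomes:

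- **Keep Y6 (weight or A1c).** H₀: α₁ ≥ Δ against H_A: α₁ < Δ. Declare non-inferiority if the upper bound of the 95% interval is below +Δ, and superiority if it is below 0.
- **Model the reduction, Y0 − Y6, for weight and for A1c.** H₀: α₁ ≤ −Δ against H_A: α₁ > −Δ. Keep the lower-bound rules as they are.

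Make the change before outcomes are seen by arm. The rule itself needs only a few sentences of wording, with no change to visits or data collection.

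The power statement in section 2.4.2.2 has to be restated with it. In the correct direction the assumed 1.6 kg deficit lies beyond the 0.33 kg margin, so the stated 80% power is not delivered on the stated inputs. The margin, the assumed difference and the sample size must be reconciled, and that costs more than the wording.

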## 2. Methods

### 2.1. Study design and overview

We will conduct a type 1 hybrid (14), randomized, controlled trial of the BRInging the Diabetes prevention program to GEriatric Populations (BRIDGE) study, which will compare an in-person DPP Tailored for Older AdulTs (DPP-TOAT) to a DPP-TOAT delivered via group virtual sessions (V-DPP-TOAT; Figure 1). All randomized individuals (*N* = 230; 1:1 randomization) will receive 22 intervention sessions over the course of a year facilitated by a certified DPP lifestyle coach, but the delivery method will vary (virtual versus in-person).

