### 2.3. Intervention arms

#### 2.3.1. Common components to both interventions: V-DPP-TOAT and DPP-TOAT

Both programs will be composed of sixteen 60-min weekly/bi-weekly sessions followed by six 60-min monthly support sessions (see Appendix B) with a group size of 8–15 facilitated by a certified DPP lifestyle coach. The DPP intervention is based on Social Cognitive Theory (20), which focuses on the role played by self-referent thought in the maintenance of behavior change. The following describes the theoretical concepts threaded throughout the intervention sessions. Self-efficacy (e.g., the participant’s confidence in their ability to engage in healthier behavior) is derived from four major sources of information: (1) mastery experiences; (2) social modeling; (3) verbal persuasion; and (4) physiological states. Mastery experiences emphasize past successes; setting incremental, easily achievable goals; identifying modifiable barriers to healthy behavior; receiving positive feedback on goal achievement; and practicing problem solving skills around barriers to adherence. Social modeling enhances mastery when participants share their successes and help each other problem-solve around barriers they encounter. Verbal persuasion emphasizes the participant’s previous successes to demonstrate their capability (e.g., “As a result of your effort, you lost a pound last week. You can do it again.”) We will assist participants in recognizing physiologic benefits they experience from lifestyle change (e.g., more energy, better sleep, or BP control). Intervention materials, which are based on the 2021 PreventT2 lifestyle change program (21), will include:*Participant Manual*: An evidence-based manual describing detailed program content and personalized calorie and macronutrient recommendations to achieve the desired weight. Written at the sixth-grade reading level in a large (14 point) sans serif font, self-assessments and goal setting procedures will be included along with approaches to self-monitor food intake, physical activity, and cooking and meal pattern guides. To enhance self-identification with the program and for ongoing visual cues for program affiliation, we will provide tote bags inscribed with the institutional logo.*Tailoring of content for aging*: Based on our prior work (22), we have adapted group sessions to the unique needs of older adults. Resources include healthful eating strategies for dentition issues, changes in taste, and special attention to interactions between food and medications. Physical activity sessions provide adaptations for physical limitations, including chair exercises and strength training.*Food Guide*: Resources developed by the United States Department of Agriculture (23) providing tailored advice for older adults will be provided, along with instructions and tips for using programs such as Healthwatch 360 (24) to track calorie and nutrient intake compared to recommendations.*Hearing Assistance*: For participants in the in-person arm, we will offer a personal amplifier (PA; PockeTalker™) to all participants to address any self-reported or suspected hearing loss. A simple PA consists of an amplifier and microphone with the amplifier feeding a speaker’s voice directly into the wearer’s ears via headphones or ear buds. These devices reduce the difficulty with hearing in “difficult listening situations” by feeding the speaker’s amplified voice directly into the patient’s ear, while headphones or ear buds muffle external sounds (i.e., signal is louder than background noise level). These devices require no professional customization; simple volume and tuning controls allow for use directly out of the box. PAs enhance communication for those who have hearing loss in a variety of clinical settings (25–27). PAs were equivalent in performance to hearing aids in one randomized controlled trial (28), sound quality of PAs was preferred over hearing aids, improved physician-patient communication for elderly hospitalized patients (29) and understanding discharge information in an Emergency Department setting (30). Participants in the virtual arm will be offered ear buds to address any self-reported or suspected hearing loss.*Videos*: Each intervention session will also feature educational and behavioral coaching videos developed by our team or reputable organizations such as the National Institutes Health and VA MOVE (Weight Management Program, supported by VA’s National Center for Health Promotion and Disease Prevention) (31). The videos last 3–5 min, and will be used to anchor the discussion. Videos will also be available on the study website for participants to review as they desire.*Smart Scales*: We will provide participants with a Renpho® (Joicom Corporation, Eastvale, CA) Smart Scale for Body Weight, Digital Bathroom Scale for self-monitoring purposes and to monitor weight given the possibility of disruptions in in-person study visits due to COVID-19 pandemic restrictions. Renpho® Scales will transmit weights to researchers automatically using BlueTooth technology and have been used in other weight management studies. A research assistant will instruct each participant during the baseline visit on using the scale to report weekly weights, providing written instructions as well as a phone number and email address to obtain technical support as needed.

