##### 2.4.2.1. Sensitivity analysis for missing data

We will compare demographic and clinical covariates in participants with and without missing data to identify factors potentially contributing to missingness. We will use 10 multiple imputations from the original dataset using the predictive mean matching method substituting missing values within each impute.

##### 2.4.2.2. Power: aim 1

To achieve 80% power to detect non-inferiority using a one-sided, two-sample *t*-test (lower bound), we will need 85 participants per group. The margin of non-inferiority is 5% of weight loss in the DPP-TOAT arm. The true efficacy difference between the 6-month weight loss is assumed to be 1.6 kg (weight loss of 5 kg in the V-DPP-TOAT arm and 6.6 kg in the in-person DPP-TOAT arm with standard deviation of 5 kg in each arm (42)). The significance level (alpha) of the test is 0.05. A total of 230 participants are needed, assuming 25% attrition at 6 months based on data from our work and others (22, 42, 43).

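### Session groups of 8–15 are nested within arm, but the primary model ignores them and looks for clustering only by clinic; if the session-group ICC is above zero, the non-inferiority interval is too narrow

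*Protocol article*

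**What the plan says.** Section 2.3.1 delivers both programmes as sessions "with a group size of 8–15 facilitated by a certified DPP lifestyle coach". Section 2.1 confirms that the virtual arm is also group-based: "DPP-TOAT delivered via group virtual sessions". Section 2.3.1 makes contact between members part of how the intervention works: "Social modeling enhances mastery when participants share their successes and help each other problem-solve around barriers they encounter".

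For Aim 1, section 2.4.2 states: "We will estimate the model using ordinary least squares regression". The model contains the baseline value, an arm indicator and one error term per participant. On clustering it says "We will assess heterogeneity in outcomes among healthcare settings/clinics by estimating an intraclass correlation coefficient (ICC"), and then "If the heterogeneity cannot be ignored, we will use a multi-level model with nested random effects", whose stated purpose is "to accommodate the correlations caused by healthcare settings/centers".

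Section 2.4.2.2 sizes the trial with a one-sided two-sample t-test ("we will need 85 participants per group") and reaches 230 after 25% attrition. It has no design effect. The Aim 2 power in section 2.4.3.3 has none either.

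**The concern.** Participants are randomised individually but treated in groups. Delivery mode defines the arm, so a session group sits wholly inside one arm. Any variation between session groups therefore enters the variance of the arm effect α₁ directly, and a model with independent errors leaves it out.

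The article does address clustering, but at the level of healthcare settings or clinics. Nothing says that session groups coincide with clinics, so a clinic random effect cannot be assumed to absorb session-group correlation. Even the clinic term is conditional on an estimated ICC, so the default is the analysis that assumes independence.

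The error would run in the direction that matters most here. An interval that is too narrow makes its lower bound clear the margin too easily, and section 2.4.2 uses the same interval for a possible superiority claim. The HbA1c analysis uses the same model. Attendance, the primary implementation outcome, is also compared between arms without a session-group term.

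**Working it through.** **Inputs from the protocol**
- 230 randomised 1:1, so 115 per arm (section 2.1).
- Group size 8–15 (section 2.3.1).
- 25% attrition at 6 months; 85 analysed per arm; one-sided alpha 0.05 (section 2.4.2.2).
- Decision rule: lower bound of the 95% interval against the margin (section 2.4.2). This is one-sided 2.5% if the interval is two-sided.

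**Assumption.** The protocol gives no session-group ICC (ρ). I use 0.02–0.05 as the range and also show 0.01.

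**The plan's own figures.** The attrition step reproduces: 85/0.75 = 113.3, so 114 per arm and 228 in total, against 230 stated. The 85 itself does not follow from the stated margin and assumed difference. That is a separate problem, and nothing below depends on it.

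**Clusters.** 115/15 = 7.7 and 115/8 = 14.4, so about 8–14 groups per arm. After attrition, the number analysed per group is m = 8 × 0.75 = 6 to 15 × 0.75 = 11.25.

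**Formulas.** Design effect DE = 1 + (m − 1)ρ. Actual one-sided error of the unadjusted analysis = 1 − Φ(z/√DE), with z = 1.960 for the 95% interval rule and z = 1.645 for one-sided 0.05.

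| m | ρ | DE | SE too small by | Error, nominal 2.5% | Error, nominal 5% |
|---|---|---|---|---|---|
| 6 | 0.02 | 1.10 | 4.7% | 3.1% | 5.8% |
| 6 | 0.05 | 1.25 | 10.6% | 4.0% | 7.1% |
| 9 | 0.01 | 1.08 | 3.8% | 3.0% | 5.7% |
| 9 | 0.02 | 1.16 | 7.2% | 3.4% | 6.3% |
| 9 | 0.05 | 1.40 | 15.5% | 4.9% | 8.2% |
| 11.25 | 0.02 | 1.21 | 8.9% | 3.7% | 6.7% |
| 11.25 | 0.05 | 1.51 | 18.7% | 5.6% | 9.1% |

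Example, last row: DE = 1 + 10.25 × 0.05 = 1.5125, √DE = 1.230, and 1 − Φ(1.960/1.230) = 1 − Φ(1.594) = 5.6%.

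**Simulation check.** I took 115 per arm, 10 groups per arm, 25% random attrition, an unadjusted two-sample t-test and 6,000 runs per setting. Error at nominal 2.5% / 5% was 2.8% / 5.1% for ρ = 0, 3.2% / 6.1% for ρ = 0.02, and 4.8% / 8.4% for ρ = 0.05. This agrees with the formula to within simulation error.

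**Aim 2, same design effects, two-sided 0.05 assumed.** With 90 per arm, dividing by DE = 1.10–1.51 leaves an effective 82–60 per arm. Power for 89% vs 63% stays at about 98–92%. Power for 82% vs 63%, stated as 80%, falls to about 78–64%.

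**The case against.** The strongest reply is that everything rests on an ICC the protocol does not give. That stands. A reader might infer that the standard errors are certainly too small; the documents do not support this. At ρ = 0 there is no inflation, and at ρ = 0.01 with 9 per group the error is 3.0% against 2.5%.

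The two alphas also differ. Set against the one-sided 0.05 of section 2.4.2.2, the 95% interval rule of section 2.4.2 exceeds 5% only near the extreme of the assumed range. The excess is over the 2.5% implied by that rule, or over 5% if the one-sided 0.05 test is used.

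A reader might also put a figure on lost Aim 1 power, such as 80% falling to 77–65%. That should not be claimed. Those values belong to a cluster-adjusted test at one-sided 0.05. The planned unadjusted test would keep about 79–75%, at the price of the inflated error. Either way, the starting 80% does not follow from the inputs of section 2.4.2.2.

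Several further inferences are not in the text: that the clinics are referring clinics or cut across arms, that the ICC check is a significance test, that membership and coach stay fixed for the year, or that group support is the main mechanism. Social modelling is one of four listed sources of self-efficacy, and the virtual arm also has one-to-one coach contact. Whether coaches work in both arms is not stated; if they do, coach effects would partly cancel in the contrast, but session-group effects would not.

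Finally, an article may leave detail to a SAP. That does not answer this point, because the article fixes a model, a clustering level and a conditional rule, and the level is not the one that delivery creates.

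**Conclusion.** The concern holds in conditional form. The plan names a clustering level, healthcare settings or clinics, and passes over the one built into delivery: the session group, nested within arm. If the session-group ICC is positive, the interval for α₁ is too narrow and false non-inferiority is more likely than nominal. Under an assumed ICC of 0.02–0.05 and about 6–11 analysed per group, the design effect is 1.10–1.51. The one-sided error is then about 3.1–5.6% under the 95% interval rule and about 5.8–9.1% under one-sided 0.05. A positive ICC is plausible because group interaction is an intended mechanism, but its size is not known from the protocol. No Aim 1 power loss should be quoted until the margin and assumed difference in section 2.4.2.2 are reconciled. For Aim 2, only the 19-point scenario is materially affected.

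**What to change.** - Record a session-group identifier for every participant. The facilitator already records attendance, so this should be available.
- In section 2.4.2, include a session-group random intercept in both arms by default, not conditional on an estimated ICC: Y6 = β₀ + α₀Y0 + α₁P + u(group) + e. Use Satterthwaite or Kenward–Roger degrees of freedom, or an equivalent small-sample cluster-robust standard error, since there are only about 8–14 groups per arm.
- Make the matching change to the attendance models in section 2.4.3.2.
- Restate the Aim 1 and Aim 2 power at N = 230 with an explicit assumed group ICC, for example 0.02 and 0.05. For Aim 1, do so after the margin and assumed difference have been reconciled.

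The cost is one data field and revised analysis text, with a somewhat wider interval, fewer degrees of freedom and a less favourable stated power. No extra enrolment is proposed. Buying back the information of 85 independent participants per arm would not be cheap: with 9 per group, 85 × 1.16 = 99 and 85 × 1.40 = 119 per arm, or 264 and 318 randomised after 25% attrition.
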